#### Sample size {14}

A previous study reports that the rate of CR after combination TACE and RFA therapy was 53% for patients with HCC tumours > 5 cm [9]. By contrast, the CR rate after TACE monotherapy was 26% for patients with intermediate-stage HCC [10]. Thus, we assume that the difference in CR rate between groups may be 28%. In this trial, we calculated that 48 patients per group are needed to achieve a two-sided α level of 0.05 and statistical power of 80%. A total of 120 patients will be included in this trial (i.e., 60 patients per group) to account for a 20% dropout rate (PASS, version 16, NCSS statistical software). Data will be analysed on an intention-to-treat basis according to patients’ originally assigned group.

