### Trial design {8}

This trial is a prospective, randomized, controlled, investigator-initiated, multi-institutional, open-blind, superiority study conducted in three academic hospitals of The Catholic University of Korea. Patient allocation will be performed with a 1:1 ratio for two parallel groups using computerized randomization.

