### Statistical methods

#### Statistical methods for primary and secondary outcomes {20a}

Parametric data will be reported as mean and standard deviation. Non-parametric data will be reported as median and range. Independent sample *t*-tests or Mann–Whitney *U* tests for continuous variables and chi-square or Fisher’s exact tests for categorical variables will be used to compare treatment groups. For the primary endpoint, rate of CR will be compared using a chi-square test. For secondary endpoints, Kaplan–Meier survival analysis and log-rank tests will be performed. A *p*-value < 0.05 will be considered statistically significant.

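### The assumed CR difference is printed as 28%, but the CR rates it is drawn from, 53% and 26%, differ by 27 points; the stated 80% power at 48 per group depends on which is meant

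*Protocol article*

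**What the plan says.** All the inputs are in the protocol article.

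- **Sample size {14}**, combination arm: "the rate of CR after combination TACE and RFA therapy was 53% for patients with HCC tumours > 5 cm".
- **Sample size {14}**, control arm: "the CR rate after TACE monotherapy was 26% for patients with intermediate-stage HCC".
- **Sample size {14}**, difference, drawn from those two rates: "Thus, we assume that the difference in CR rate between groups may be 28" per cent.
- **Sample size {14}**, resulting size: "48 patients per group are needed to achieve a two-sided α level of 0.05 and statistical power of 80" per cent.
- **Sample size {14}**, inflation: "A total of 120 patients will be included in this trial (i.e., 60 patients per group) to account for a 20% dropout rate".
- **Trial design {8}**, allocation: 1:1.
- **Statistical methods {20a}**, primary analysis: "rate of CR will be compared using a chi-square test".

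The sample size section names the software (PASS) but not the test or variance option used in the calculation. Section {20a} names no continuity correction for the primary test.

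**The concern.** The sentence stating the difference begins as a deduction from the two rates before it, yet 53 − 26 is 27, not 28. A reader cannot tell which figure was entered in the calculation: the two printed rates, a rounded difference, or unrounded rates that are not shown.

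The effect size and the power are the two figures on which the trial's size rests. One percentage point is little, but 48 per group sits close to the 80% boundary. Whether the planned chi-square test reaches 80% at that size depends on whether the effect is 27 or 28 points. What is at stake is the accuracy of the power statement, not whether the trial is viable.

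**Working it through.** **Inputs.** p1 = 0.53, p2 = 0.26, two-sided α = 0.05 (z = 1.960), power 80% (z = 0.842), 1:1 allocation, 20% dropout. Let d = p1 − p2 and p̄ = (p1 + p2)/2.

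**1. The difference.** 0.53 − 0.26 = 0.27. The plan prints 28%.

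**2. Reproducing the 48 (unpooled formula).** n = (1.960 + 0.842)² × [p1(1−p1) + p2(1−p2)] / d²

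= 7.849 × (0.2491 + 0.1924) / 0.0729 = 47.5, so 48 per group. The plan's figure is reproduced.

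**3. Pooled formula, which matches the uncorrected chi-square test.** n = [1.960·√(2p̄(1−p̄)) + 0.842·√(p1(1−p1) + p2(1−p2))]² / d²

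| Rates | Difference (points) | Unrounded n | n per group |
|---|---|---|---|
| 53% vs 26% (as printed) | 27 | 50.3 | 51 |
| 54% vs 26% | 28 | 46.9 | 47 |
| 53% vs 25% | 28 | 46.4 | 47 |
| 53.3% vs 25.6% (assumed) | 27.7 | 47.7 | 48 |

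For the first row: p̄ = 0.395, so [1.960 × 0.6913 + 0.842 × 0.6645]² / 0.0729 = (1.3550 + 0.5592)² / 0.0729 = 50.3.

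The last row is an assumption, because the plan gives no unrounded rates. Those rates would print as 53% and 26%, and their difference as 28%.

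**4. Power of the uncorrected chi-square test.** Power = Φ{[d√n − 1.960·√(2p̄(1−p̄))] / √(p1(1−p1) + p2(1−p2))}. For 53% vs 26% at n = 48: (0.27 × 6.928 − 1.3550)/0.6645 = 0.776, and Φ(0.776) = 78.1%. The exact column enumerates both binomial distributions.

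| Rates | n per group | Normal approximation | Exact |
|---|---|---|---|
| 53% vs 26% | 48 | 78.1% | 78.2% |
| 53% vs 26% | 50 | 79.8% | 80.5% |
| 53% vs 26% | 60 | 86.6% | 86.8% |
| 54% vs 26% | 48 | 81.0% | 81.1% |
| 53% vs 25% | 48 | 81.3% | 81.4% |

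The 51 in step 3 is therefore the formula's answer; by exact enumeration, 50 per group already passes 80%.

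**5. Dropout.** 48 / (1 − 0.20) = 60 per group, 120 in total, as the plan states. With 60 enrolled per group, 51 evaluable corresponds to 15% dropout (51 / 0.85 = 60).

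**The case against.** The strongest reply is that this is a rounding artefact. If the source rates were, say, 53.3% and 25.6%, then 53%, 26%, 28%, 48 per group, 80% power and the chi-square test would all come from one ordinary pooled calculation. That stands as a possibility. A reader might infer from the mismatch that the printed figures cannot belong to a single calculation; the plan does not support that inference. Nor does it confirm the rounding explanation, because the unrounded rates are not given. The paragraph as printed still needs correcting or explaining.

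It can also be said that 48 is a legitimate result for 53% vs 26%, since the unpooled formula is an accepted planning method. This stands too: the gap between 48 and 51 is a choice between two standard variance formulas. The 78% is nevertheless the power of the test named in section {20a} at the printed rates.

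A reader might go further and quote the lower power of a continuity-corrected chi-square or Fisher's exact test. Section {20a} mentions Fisher's test only in its general sentence on categorical variables. For the primary endpoint it names a chi-square test with no correction, so such figures would describe an analysis the plan does not specify.

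**Conclusion.** The point holds in a limited form and is minor. The printed difference does not equal the difference of the printed rates.

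If 53% and 26% are the design rates, the stated 80% power at 48 evaluable per group is about 78% for the uncorrected chi-square test, a shortfall of just under 2 points (80 − 78.2 = 1.8). If the true design difference is 28 points, power is about 81% and the statement is sound.

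A reader might conclude that the trial is underpowered. The documents do not support that. The 78% applies only if the full 20% allowed for dropout is lost. The sample size section commits to intention-to-treat analysis, and if all 60 per group contribute an observed response, power at 53% vs 26% is about 87%. That is the upper end, since patients whose response is imputed add less information than those observed.

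These figures assume two-sided α = 0.05, 1:1 allocation and no continuity correction.

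**What to change.** In Sample size {14}, either correct the difference to 27%, or print the unrounded CR rates that give 28%. The authors know which applies; the document does not show it.

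If 53% and 26% are the design rates, also restate the power in one of two ways:

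- about 78% with 48 evaluable per group and about 87% with all 60 analysed; or
- 80% with 51 evaluable per group, which lowers the dropout that 60 per group can absorb from 20% to 15%.

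If the unrounded rates do give about 27.7 points, the 48 and the 80% can stay. A clause naming the test and variance option used in PASS would settle the question for readers.

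The cost is wording only. The total of 120, the allocation and the primary test are unchanged. Under the first correction, the stated power or the tolerated dropout becomes slightly less favourable.

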#### Recruitment {15}

Patients with beyond-the-Milan criteria HCC will be considered as candidates for trial enrolment in concordance with the inclusion and exclusion criteria. Written informed consent will be obtained from each patient. A total of 120 patients will be enrolled from the three hospitals by competitive recruitment.

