**Methods:**

A total of 120 patients with beyond-the-Milan criteria HCC who have viable tumour after first TACE will be enrolled in this multi-institutional, parallel, pragmatic, randomized controlled trial. Patients with metastasis, vascular invasion, or a sum of tumour diameter > 8 cm will be excluded. Eligible patients will be randomly assigned to combination TACE and RFA therapy or TACE monotherapy groups. Patients in the combination therapy group will receive a second TACE and subsequent RFA at the viable tumour. Patients in the TACE monotherapy group will receive only second TACE. Patients in both groups will undergo magnetic resonance imaging 4–6 weeks after second TACE. The primary endpoint is 1-month tumour response, and secondary endpoints are progression-free survival, overall response rate, number of treatments until CR, overall survival, and change in liver function.

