### Intervention description {11a}

#### Before allocation

Patient eligibility will be evaluated after the first TACE. Patients with viable HCC after first TACE will be included in the trial. First TACE will be performed with ethiodized oil or drug-eluted beads with adriamycin (50–100 mg depending on tumour volume or liver function). The selection of ethiodized oil versus drug-eluted beads will be determined by discussion among physicians and interventional radiologists. All feeding arteries will be treated via superselective catheterization. Gelfoam particles will be used with ethiodized oil as is conventional for TACE.

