## Discussion

In this trial, we will assess the efficacy of combination TACE and RFA therapy versus TACE monotherapy for patients with viable beyond-the-Milan criteria HCC after first TACE. Treatment of beyond-the-Milan criteria HCC still poses a great clinical challenge [13]. Barcelona Clinic Liver Cancer guidelines suggest that intermediate-stage HCC can be treated with TACE and that advanced-stage (portal invasion, N1, or M1) patients can be treated with sorafenib [2]. For beyond-the-Milan criteria patients, TACE alone is often not effective, as tumours tend to have multiple feeders, and a high tumour burden demands a large amount of embolic material, which can lead to incomplete treatment due to a risk of hepatic failure. Although sorafenib and new-generation systemic chemotherapies are reserved for patients with more advanced-stage disease, further improvements in response rates may not be expected [14]. Thus, it seems necessary to establish a more stratified treatment strategy for patients with intermediate but beyond-the-Milan criteria HCC.

Recent studies on combination TACE and RFA therapy for early- and intermediate-stage HCC demonstrate promising results compared with TACE or RFA alone [4, 6, 7, 15–17]. Theoretically, this combination therapy can overcome the limitations of each individual treatment. First, TACE can reduce tumour burden. Second, ablation could be more effective without heat sinking by decreasing arterial flow through embolization. Third, TACE can cover undetectable satellite nodules that can be missed by RFA [17]. In addition, lipiodol-uptake nodules after TACE can be precisely localized during RFA in the treatment of non-ultrasound-discernible and inaccessibly located HCC [18]. Whereas most studies on combination therapy concerned tumours sized < 5 cm, it is unclear whether combination therapy could also be beneficial for beyond-the-Milan criteria patients.

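### The printed inclusion list does not carry the stated population: nothing in it requires disease beyond Milan, and its viability item covers only two of the three nodule categories

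*Protocol article*

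**What the plan says.** The protocol article describes one population throughout. The abstract states that "A total of 120 patients with beyond-the-Milan criteria HCC who have viable tumour after first TACE will be enrolled". The Objectives and Recruitment sections name beyond-the-Milan HCC, and Recruitment ties this to the list: "Patients with beyond-the-Milan criteria HCC will be considered as candidates for trial enrolment in concordance with the inclusion and exclusion criteria". The Discussion describes a comparison "for patients with viable beyond-the-Milan criteria HCC after first TACE".

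The Inclusion criteria set tumour burden in three items: a single nodule of 5–8 cm, two nodules with a maximal size of at most 8 cm, and three nodules with a maximal size of at most 5 cm. The next item asks for viable HCC after first TACE in patients who meet criteria (2) or (3). Elsewhere viability is not tied to nodule number. Before allocation says "Patients with viable HCC after first TACE will be included in the trial", and the Allocation and Outcomes sections likewise speak of patients with viable tumour after first TACE.

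**The concern.** A population described as beyond a criterion needs a lower bound on tumour burden. The list prints one for a single nodule and none for two or three nodules. The Exclusion criteria supply none either. A patient with several small nodules can therefore satisfy every printed item without having the disease that the trial is about.

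The viability item has a separate fault. It names two criteria where there are three nodule categories, so the list and the treatment sections disagree about whom the viability requirement covers.

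What is at stake is first the meaning of the result, which will be reported as evidence for beyond-the-Milan disease and should come from patients who have it. Second, the planning rate for the combination arm comes from large tumours. If smaller tumours were enrolled and responded differently, the CR contrast could shrink.

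**Working it through.** **1. The list against the stated population.** The item numbers were lost when the text was read, so they are counted here in printed order.

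| Item | Lower size limit | Upper size limit | Named in the viability item |
|---|---|---|---|
| (2) single nodule | 5 cm | 8 cm | yes |
| (3) two nodules | none | 8 cm | yes |
| (4) three nodules | none | 5 cm | no |

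- Two nodules of 1 cm satisfy (3), and three nodules of 1 cm satisfy (4).
- No other inclusion item and no exclusion item mentions Milan or sets a minimum size.
- The abstract adds "Patients with metastasis, vascular invasion, or a sum of tumour diameter > 8 cm will be excluded". This is a further upper limit, so it does not close the gap.
- Calling those small-nodule patients within Milan assumes the usual multinodular limit (each nodule at most 3 cm). The protocol prints no Milan limit. The gap does not depend on that figure, because any lower bound would be missing.

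**2. The viability item.** Under any numbering, a reference to two criteria cannot cover three nodule categories. By order the omitted one is three nodules. Read literally, such patients either can never satisfy the viability item, which leaves (4) empty, or are exempt from it. The first reading conflicts with (4). The second conflicts with the Before allocation, Allocation and Outcomes sections.

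**3. The plan's own sample size.** From Sample size: "the rate of CR after combination TACE and RFA therapy was 53% for patients with HCC tumours > 5 cm", "the CR rate after TACE monotherapy was 26% for patients with intermediate-stage HCC", and "48 patients per group are needed to achieve a two-sided α level of 0.05 and statistical power of 80"%. With the unpooled-variance formula:

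n = (1.960 + 0.842)² × (0.53×0.47 + 0.26×0.74) / (0.53 − 0.26)²
= 7.849 × 0.4415 / 0.0729 = 47.5, hence 48 per group.

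Allowing for 20% dropout, 48 / 0.80 = 60 per group, or 120 in total. The plan's numbers reproduce and are not at issue.

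**4. What a mixture could do to power (illustration only).** Let s be the share of within-Milan patients. The CR rate in each arm is then

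p = (1 − s) × planning rate + s × within-Milan rate.

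Example with s = 0.30 and within-Milan CR of 70% (combination) versus 60% (TACE alone):
- combination 0.7×0.53 + 0.3×0.70 = 0.581
- TACE alone 0.7×0.26 + 0.3×0.60 = 0.362
- difference 21.9 points instead of 27

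Power is from exact binomial enumeration of the uncorrected two-sided chi-square test at 0.05. The table gives it for s = 10 / 20 / 30%. The shares and the within-Milan rates are assumptions; the documents give neither.

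| Within-Milan CR, combination vs TACE | 48 per group | 60 per group |
|---|---|---|
| none enrolled (base, 53% vs 26%) | 78% | 87% |
| 70% vs 50% | 75 / 73 / 70% | 85 / 82 / 80% |
| 70% vs 60% | 72 / 65 / 59% | 82 / 76 / 69% |
| 80% vs 53% (same 27-point difference) | 78 / 77 / 77% | 86 / 86 / 86% |

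**The case against.** The strongest reply is that the protocol, read as a whole, leaves no doubt about whom it wants. Recruitment makes beyond-the-Milan HCC the candidate pool and then applies the list, so a patient must satisfy both. Hepatologists do the screening, for a trial whose title names Milan. Viable tumour on CT is stated again at the point of allocation, and RFA is aimed at the viable portion. On this view the viability item holds a slip in a cross-reference. Most of this stands: the intent can be recovered. What remains is that Recruitment points back to a list that omits the condition, and that the list contradicts other sections on viability.

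A reader might infer more, and three stronger readings are not supported.

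- **Three-nodule patients will be handled differently between sites, or randomised without viable tumour.** The Before allocation and Allocation sections ask for viable tumour whatever the nodule number, and nothing in the document shows sites diverging.
- **The loophole admits patients whom earlier studies already covered.** The abstract and the Background describe those studies as mostly of small single tumours. They do not say that small multinodular disease was covered.
- **The trial will be badly underpowered.** A large loss needs a sizeable within-Milan share with high CR on TACE alone and little or no benefit from RFA. That is an extreme case for patients who still have viable tumour after a first TACE, and the documents give no share or rate to support it.

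**Conclusion.** The inconsistency is real and lies in the wording of the Inclusion criteria. Followed literally, the list does not select the population named in the abstract, Objectives, Recruitment and Discussion, and its viability item leaves out one nodule category. That mismatch carries the point. It holds whatever the multinodular Milan limit is; only the labelling of particular patients as within Milan rests on the assumed limit.

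Power is secondary and conditional. In the scenarios shown the loss runs from almost none to about 20 points at 48 per group (78% to 59%) and about 18 points at 60 per group (87% to 69%). Where in that range the trial would fall, or whether any such patients would be enrolled at all, cannot be judged from the documents. The list should be corrected because recruitment is still open (completion is expected around June 2026) and the correction is small.

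**What to change.** Reconcile the Inclusion criteria with the abstract, Before allocation, Allocation and Recruitment:

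1. Add an inclusion item, for all nodule counts, that the tumour exceeds the Milan criteria on imaging before first TACE. Print the sponsor's own limit for two and three nodules, as is already done for one.
2. Make the viability item refer to all three nodule categories.
3. Record Milan status before first TACE on the e-CRF, including for patients already randomised.
4. Keep all randomised patients in the intention-to-treat analysis, and report CR in the beyond-Milan subset as a sensitivity analysis. The subset is defined before randomisation, so the comparison within it is still a randomised one.

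The cost is a short eligibility amendment and one e-CRF field. The downside is slightly fewer eligible multinodular patients, and so marginally slower accrual.

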### Assignment of interventions: allocation

#### Sequence generation {16a}

An independent statistician will generate random numbers using STATA (ver. 16, StataCorp LLC) using a 1:2 to 1:6 random block stratified by three strata (i.e., hospitals). Data will be stored in a secure online database (i.e., REDCap) using electronic case report forms (e-CRFs).

#### Concealment mechanism {16b}

Informed consent will be obtained at the hepatology outpatient clinic. After agreeing to participate in the trial, patients will be admitted to the hospital based on its interventional radiology schedule. Random allocation will be performed on the day of second TACE. An outpatient hepatology clinic nurse who is independent from this trial will access the secure, password-protected, online database (i.e., REDCap) to perform patient allocation and notify the hepatologist only. All researchers and patients will be blinded to allocation status except for the hepatologist. Patient allocation will be released after the completion of second TACE.

#### Implementation {16c}

An independent statistician ([name]) will generate a stratified computer-generated block randomization list using STATA. A hepatologist will screen patients on an outpatient basis. If a patient agrees to participate in the trial, then the hepatologist will register the patient in the online database. Patients will be admitted to the hospital the day before second TACE. Second TACE will be performed by a dedicated interventional radiologist. After second TACE, patient allocation will be opened. According to their allocation, patients will be subsequently treated with RFA or discharged from the hospital.

### Assignment of interventions: blinding

#### Who will be blinded {17a}

The interventional radiologist and patients will be blinded to patient allocation before second TACE and unblinded after second TACE. The independent outcome assessors will be blinded to patient allocation. The primary outcome (i.e., CR) will be assessed by comparing initial and follow-up MRIs.

#### Procedure for unblinding if needed {17b}

After allocation, patients and the interventional radiologist performing second TACE will be blinded. After second TACE, the hepatologist will reveal patient allocation.

### Data collection and management

#### Plans for assessment and collection of outcomes {18a}

Consistent with the usual treatment course for HCC, initial laboratory tests and MRI will be performed. Tumour marker assessment (i.e., alpha-fetoprotein and protein induced by vitamin K absence-II) and MRI will also be performed 1 month after treatment. Blood laboratory tests and CTs will be performed depending on patients’ medical conditions as decided by the physician.

#### Plans to promote participant retention and complete follow-up {18b}

Patients will receive a recommendation to continue follow-up care at their treating hospital. There are no plans to promote participation retention.

